## 7. SAFETY / ADVERSE EVENTS

In the previous CAMPER trial, there were no documented cases of CSF leakage, headache, neurologic deterioration, or meningitis attributable to the insertion, presence, or withdrawal of the lumbar intrathecal catheter. **In this CASPER trial, patients will have the intrathecal catheter inserted as part of their clinical management.** However, as part of the clinical follow-up of participants enrolled in CASPER, we will document AEs related to the insertion, presence, or withdrawal of the lumbar intrathecal catheter, and also related to the drainage of CSF to lower ITP. These specific AEs are described further in Section 7.3.

The AE reporting period will be defined as commencing from the time of insertion of the intrathecal catheter until 24 hours after its removal. If an AE is ongoing at the time of catheter removal, it will be monitored until resolution or until 30 days have elapsed.

A review and sign-off by the local Principal Investigator of any AEs related specifically to the presence of the intrathecal catheter will occur for each individual patient at the end of the 24 hours following intrathecal catheter removal. A data safety monitoring board will be established to perform an interim analysis of all complications related to insertion and presence of a lumbar intrathecal catheter and will convene after the first 10 patients enrolled, and then again after 50 patients have been enrolled.

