**Objective 4.** To determine if there are complications associated with the installation of the intrathecal catheter and drainage of CSF in the acute SCI patient.

It goes without saying that we will measure AEs associated with intrathecal catheter placement. Of course, acute SCI patients incur a huge number of AEs; but we have utilized a system of daily monitoring those that are most applicable to the lumbar catheters – namely CSF leak/postural headache, nausea/vomiting, and infection. The patients will be carefully monitored by the study research team throughout the time that they have the intrathecal catheter placed.

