### 7.1. Defining, Grading and Recording of AEs

#### 7.1.1. Definition of an AE & Serious Adverse Event (SAE)

An **AE** is defined as any untoward medical occurrence in a patient or clinical investigation participant undergoing a medical intervention and which does not necessarily have a causal relationship with the treatment. An AE can therefore be any unfavorable and unintended sign (including an abnormal laboratory finding, for example), symptom, or disease temporally associated with the medical intervention, whether or not it is considered related to the medical intervention. For purposes of this study, AEs will be defined as a change from the patient's baseline that occurs in temporal relationship to any study related procedures (i.e. insertion of the intrathecal catheter or drainage of CSF).

An **SAE** is defined as any untoward medical occurrence that:

- results in death,
- is life-threatening,

*Note: the term "life-threatening" refers to an event in which the patient was at risk of death at the time of the event; it does not refer to an event which hypothetically might have caused death if it were more severe.*

- requires inpatient hospitalization or prolongation of existing hospitalization,
- results in persistent or significant disability/incapacity,
- is a congenital anomaly/birth defect,

- is a medically important event or reaction that may not be immediately life-threatening or result in death or hospitalization, but may jeopardize the patient or may require intervention to prevent one of the other outcomes listed above.

Medical and scientific judgment should be exercised in deciding whether expedited reporting is appropriate in other situations, such as important medical events that may not be immediately life-threatening or result in death or hospitalization but may jeopardize the patient, or may require intervention to prevent one of the other outcomes listed in the definition above.

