### 7.1.3. Recording of AEs

All AEs that occur during the reporting period, insertion of catheter to 24 hours post-removal, will be recorded in the Adverse Event case report forms. AE data will be obtained from any information volunteered by the patient or through patient questioning. Both the passive system of recording AEs and directed inquiry regarding known potential side effects of insertion and presence of the lumbar intrathecal catheter (see below) will be utilized. Additional information to be recorded includes the **duration** of the AE (onset/resolution dates), **severity**, **relationship** to the insertion and presence of the lumbar intrathecal catheter or drainage of CSF (classified as “probable”, “possible”, “unlikely” or “unrelated” - see below) and any **concomitant treatment** dispensed (or other action taken). All “serious” and “unexpected” AEs will be reported to the local REB as per local institutional guidelines. Additionally, the ‘Serious and Unexpected’ Adverse Events will be reported to the CASPER Project Manager.

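### Section 7 gives two different rules for which adverse events are captured, and its investigator sign-off and board review name neither CSF drainage, catheter withdrawal nor events judged unrelated

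*Protocol*

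**What the plan says.** Three activities need separating: what is captured, what the local investigator signs off, and what the board analyses.

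**Capture.** The opening of Section 7 states that "we will document AEs related to the insertion, presence, or withdrawal of the lumbar intrathecal catheter, and also related to the drainage of CSF". Section 7.1.1 defines an adverse event broadly, "whether or not it is considered related to the medical intervention", and its study-specific definition asks only for a link in time to the catheter insertion or the drainage. Section 7.1.3 then says that "All AEs that occur during the reporting period, insertion of catheter to 24 hours post-removal, will be recorded". It lists relationship as one of the items recorded for each event, with unlikely and unrelated among the permitted ratings.

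**Sign-off.** Section 7 provides for "A review and sign-off by the local Principal Investigator of any AEs related specifically to the presence of the intrathecal catheter" once 24 hours have passed since catheter removal.

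**Board.** Section 7 sets up a data safety monitoring board to perform an "interim analysis of all complications related to insertion and presence of a lumbar intrathecal catheter". The board "will convene after the first 10 patients enrolled, and then again after 50 patients have been enrolled".

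**Other routes.** Section 7.1.4 sends every serious event, whatever its attribution, to the Project Manager and the site's ethics board. It does not mention the monitoring board. Objective 4 in Section 3 asks about complications of both the catheter and the drainage.

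**The concern.** There are two problems.

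First, relatedness is an entry condition in the opening of Section 7 but a data field in Sections 7.1.1 and 7.1.3. A coordinator working from the opening would leave off an event judged unrelated. One working from Section 7.1.3 would record and rate it. Complication rates could then differ between sites for reasons that have nothing to do with safety, and an event never recorded cannot be recovered at analysis.

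Second, even if Section 7.1.3 governs everywhere, review is narrower than capture. Sign-off and the board's analysis depend on attribution, and the exposures they name leave out drainage and withdrawal. Drainage is what is new here. Section 2.4 says CAMPER took no active measures to lower pressure by draining CSF, so its clean safety record says nothing about drainage harms. The earlier randomised trial in Section 2.3 allocated 12 patients to drainage and removed less than 120 ml from each over 72 hours. CASPER is therefore where drainage harms would be expected to show, and the board's written remit does not name them.

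**Working it through.** No sample size, power or event count in the protocol bears on this, so there is no figure to reproduce. The check is a comparison of the text, followed by a labelled illustration.

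**Step 1. Exposure named at each step.**

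| Protocol place | Must the event be related? | Insertion | Presence | Withdrawal | Drainage |
|---|---|---|---|---|---|
| Section 3, Objective 4 | Associated | yes | no | no | yes |
| Section 7 opening, documentation | Yes | yes | yes | yes | yes |
| Section 7.1.1, study definition | No, link in time only | yes | no | no | yes |
| Section 7.1.3, recording | No, all events in the window | – | – | – | – |
| Section 7.1.3, relationship field | Rated after recording | yes | yes | no | yes |
| Section 7.2, heading | – | yes | yes | yes | yes |
| Section 7.2, definitions | – | yes | yes | no | no |
| Section 7, sign-off | Yes | no | yes | no | no |
| Section 7, board analysis | Yes | yes | yes | no | no |

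The Section 7.2 definitions do mention withdrawal or removal of the catheter, but as evidence of response when the exposure stops, not as an exposure that might cause harm.

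**Step 2. What follows.** Rows 2 and 4 state different capture sets. The last two rows are narrower than every capture rule. Read literally, an event correctly attributed to drainage falls outside both sign-off and the board's analysis.

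**Step 3. Illustration of a relatedness filter.** Inputs:

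- p, the true rate of a catheter complication. Section 7.3.4 estimates meningitis at about 1%. The highest infection rate it cites, from a lumbar drainage series, is 13/312 = 4.2%.
- m, the share of true events judged unrelated. The protocol gives no value. I assume 0%, 25% and 50%.
- n, patients at each board meeting: 10 and 50 (Section 7).

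The chance that a board shown only related events sees at least one is 1 − (1 − p(1 − m))^n.

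| p | n | m = 0% | m = 25% | m = 50% |
|---|---|---|---|---|
| 1% | 10 | 9.6% | 7.3% | 4.9% |
| 1% | 50 | 39.5% | 31.4% | 22.2% |
| 4.2% | 10 | 34.9% | 27.4% | 19.1% |
| 4.2% | 50 | 88.3% | 79.8% | 65.4% |

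For example, at p = 1%, m = 50% and n = 50: 1 − (1 − 0.005)^50 = 0.222.

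**The case against.** The defence has several good points.

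- The opening of Section 7 can be read as naming events of special interest, since it points to Section 7.3 for their description, with Sections 7.1.1 and 7.1.3 as the operative rules. That is plausible and is the reading I would adopt. But the protocol does not state it, so a wording conflict remains.
- A reader might infer that misattributed harms drop out of Objective 4. The documents do not support this. Under Section 7.1.3 such events stay on the case report form with their rating, and nothing limits the Objective 4 analysis to related events.
- A reader might infer that such events never reach the board. That is also too strong. Section 7 states the board's purpose, not an exclusive data feed. A charter may exist, and serious events go to the Project Manager and ethics board regardless of attribution.
- Competing causes do not by themselves remove an event. Under Section 7.2 an event with a reasonable time sequence and another possible explanation is rated possible, and unrelated is reserved for events that cannot be linked at all. This limits misattribution if the scale is applied as written.
- Some harms are detected without attribution: daily neurological examination (Section 6.1), directed inquiry (Section 7.1.3), and CSF surveillance under hospital protocols (Section 7.3.4).
- Objective 4 says "we have utilized a system of daily monitoring those that are most applicable to the lumbar catheters". A reader might take this as a narrower capture rule. It fits equally well as a targeted daily check on top of general recording.
- No section says who assigns relatedness, so it cannot be claimed that the team that chose the catheter judges its own complications.
- Drainage needs a catheter in place, so a generous reader could count drainage harms under presence. However, the Section 7 opening and Section 7.1.3 list drainage separately from presence, so the protocol itself treats them as distinct.

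What remains is the conflict over capture, the omission of drainage and withdrawal from sign-off, definitions and board remit, and the lack of any stated route to the board for events judged unrelated.

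**Conclusion.** The point holds in two parts. The protocol states two capture rules that sites could apply differently. Independently of that, the written scope of sign-off and of board review is narrower than either rule: it depends on attribution and omits drainage and withdrawal. On this text the board has no stated means of re-examining attribution, and a harm correctly attributed to drainage lies literally outside its analysis.

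The size cannot be fixed from the protocol. At its 1% meningitis estimate, moving from no misattribution to 50% lowers the chance that a board shown only related events sees a case by 50 patients from 39.5% to 22.2%. At 4.2% it falls from 88.3% to 65.4%. These figures assume independent patients, a board that sees only related events, and misattribution shares that are mine. Meningitis also has explicit criteria in Section 7.3.4, so it may be less open to misattribution than headache or nausea. The omission of drainage rests on wording alone and needs no such assumption.

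This should be corrected, because it affects safety oversight and the answer to Objective 4. It does not show that events have been or will be lost.

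**What to change.** 1. Make Section 7.1.3 the single recording rule, and reword the opening of Section 7 so that the catheter and drainage events are events of special interest within it.
2. Extend investigator sign-off, the Section 7.1.3 relationship field, the Section 7.2 definitions and the board's remit so that each covers insertion, presence, withdrawal and CSF drainage. State who assigns relatedness.
3. Give the board all adverse events and all serious adverse events at each meeting, tabulated by type and by relationship, including those rated unlikely and unrelated.
4. Report Objective 4 for all adverse events in the window alongside the related subset.

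The cost is protocol wording, case report form guidance and modest extra recording at sites that had followed the narrow rule. No new assessment or visit is needed.

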### **Specific Aims**

This multicenter study will enroll 100 patients with acute traumatic cervical and thoracic SCI who have a lumbar intrathecal catheter inserted within 48 hours of their injury. The lumbar intrathecal catheter will be inserted pre-operatively for the measurement of ITP and the collection of cerebrospinal fluid (CSF) samples. SCPP will be calculated as the difference between MAP and the ITP.

There are two important distinct yet related objectives in this prospective interventional study.

1. Determine the effect of SCPP maintenance  $\geq 65$  mmHg in acute SCI on neurologic recovery as measured by ASIA Impairment Scale (AIS) grade conversion and motor score improvement.
2. Collect CSF and blood samples for the measurement of neurochemical biomarkers and storage for future biomarker discovery and validation studies.

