#### **7.1.4. SAE Reporting**

All SAEs that occur during the course of the study must be reported to the CASPER Study Project Manager by telephone within 24 hours of the site becoming aware of the event. When appropriate, the SAE will be documented on the “Serious and Unexpected Adverse Event” case report form and submitted to the CASPER Study Project Manager within 48 hours. All SAEs must be reported to the site’s REB according to the local requirements.

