#### **7.3.4. Meningitis**

In Grady's series of 513 patients, one patient reportedly developed meningitis (0.2% incidence) but this was attributed to the transsphenoidal hypophysectomy that the patient had undergone [30]. Cheung and colleagues described two patients out of 162 (1.2%) who developed meningitis after having CSF drainage during thoracoabdominal aortic repairs; one who developed it after the drain was removed, and the other whose catheter fractured off [36]. Coplin and colleagues reviewed 312 patients undergoing lumbar CSF drainage and found an infection rate of 4.2% (13 of 312) [37]. Two-thirds of these patients had already undergone previous CSF drainage procedures or had persistent CSF fistulae, implying that their risk of infection was already higher with a previously "exposed" CSF space. All lumbar drain infections were treated successfully with antibiotic therapy and without neurological deficit. The lumbar intrathecal catheter will remain in situ for up to 7 days for the purpose of intrathecal pressure and spinal cord perfusion pressure monitoring and collection of CSF samples every 8 hours. It is not unreasonable to expect a lower infection rate in SCI patients that have neither CSF fistulae nor a previous drainage procedure. ***The estimated risk of meningitis due to insertion and presence of the lumbar intrathecal catheter is therefore approximately 1%.***

Clinical surveillance of the CSF will be done as per the institutional protocols. At Vancouver General Hospital, a 1 ml sample of CSF is sent daily to the lab for gram stain, cell count, and bacterial culture. We know that the injury itself will induce some meningeal inflammation and elevate the cell count and protein levels; in this regard, the gram stain and bacterial culture will be the critical components of this evaluation. In addition, vital signs of patients will be continuously monitored by nursing staff. A fever of  $\geq 38.5^{\circ}\text{C}$  within 24 hours of a positive CSF culture and in the absence of other concurrent infection will be considered to be supportive of the diagnosis of meningitis. If meningitis becomes evident (positive bacterial culture, positive gram stain, and an associated fever of  $\geq 38.5^{\circ}\text{C}$ ), it is expected that the patient will be started on the appropriate antibiotics and the lumbar intrathecal catheter discontinued.

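### The safety board has no scheduled look after patient 50 and no written SAE route reaches it, so half of the planned patients have no assigned independent cross-site safety review

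*Protocol*

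**What the plan says.** **Board schedule and remit (Protocol section 7).** The board is to "perform an interim analysis of all complications related to insertion and presence of a lumbar intrathecal catheter", and it "will convene after the first 10 patients enrolled, and then again after 50 patients have been enrolled". No later meeting and no out-of-schedule trigger is described. Specific Aims gives the size: "This multicenter study will enroll 100 patients with acute traumatic cervical and thoracic SCI".

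**What is collected (section 7).** Adverse events (AEs) are documented for the catheter "and also related to the drainage of CSF to lower ITP". The reporting period runs from catheter insertion to 24 hours after removal. The local investigator signs off catheter-related AEs for each patient at the end of that period.

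**Reporting routes.**
- Section 7.1.3: all AEs in the period go on case report forms. Those that are both serious and unexpected go to the local ethics board, and in addition "the ‘Serious and Unexpected’ Adverse Events will be reported to the CASPER Project Manager".
- Section 7.1.4: all SAEs "must be reported to the CASPER Study Project Manager by telephone within 24 hours of the site becoming aware of the event". A form whose title is limited to serious and unexpected events follows within 48 hours, but only where appropriate. All SAEs also go to the site's ethics board under local rules.
- Section 9: sites see only their own data. The lead investigator's team can access de-identified data from every site.

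**The concern.** The protocol's safety argument leans on the absence of catheter complications in CAMPER (sections 7 and 7.3.5). CAMPER did not drain CSF to change pressure (section 2.4) and kept catheters in for up to 5 days. CASPER drains actively and keeps catheters in for up to 7 days, and section 7.3.5 itself expects meningitis risk to rise with time in place. Finding complications of the catheter and of drainage is Objective 4. Pooled independent review therefore matters here, yet as written it stops at the halfway point.

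Three smaller features add to this:
- The looks are counted by enrolment, so the first can fall while the most recent patients still have catheters in place.
- The SAE routes do not reach the board, and the two sections use different criteria for central reporting.
- The board's remit names catheter insertion and presence but not drainage, the main new element of management.

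At stake is how soon a small number of related events, spread over several sites, would be put in front of an independent body.

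**Working it through.** The protocol gives no operating figure for the board schedule, so there is none to reproduce. The two cited infection rates do check: 13/312 = 4.17% (stated as 4.2%) and 2/162 = 1.23% (stated as 1.2%), both in section 7.3.4.

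**Inputs.** Looks at 10 and 50 enrolled (section 7); 100 patients (Specific Aims); meningitis risk about 1%, and the 4.2% series (both section 7.3.4). Assumed: independent patients and a constant risk p.

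**Gaps.** 50 − 10 = 40 patients between looks. 100 − 50 = 50 patients after the last look, which is 50% of enrolment.

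**Chance of cases in a gap of n patients.** P(at least 1) = 1 − (1−p)^n. P(at least 2) = 1 − (1−p)^n − n·p·(1−p)^(n−1).

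| Patients | n | p | Expected cases | P(≥1) | P(≥2) |
|---|---|---|---|---|---|
| 11–50 | 40 | 1% | 0.4 | 33.1% | 6.1% |
| 11–50 | 40 | 4.2% | 1.7 | 82.0% | 50.5% |
| 51–100 | 50 | 1% | 0.5 | 39.5% | 8.9% |
| 51–100 | 50 | 4.2% | 2.1 | 88.3% | 62.7% |

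For the third row: 0.99^50 = 0.6050, so P(≥1) = 0.395; and 50 × 0.01 × 0.99^49 = 0.3056, so P(≥2) = 1 − 0.6050 − 0.3056 = 0.089.

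**What the first look can show.** With 0 events in 10 complete patients, the exact two-sided 95% upper limit is 1 − 0.025^(1/10) = 30.8%. The chance of any case among the first 10 is 1 − 0.99^10 = 9.6% at 1%.

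**Timing.** The catheter stays up to 7 days (section 5.5) and the reporting period adds 24 hours, so a patient's safety period can last about 8 days. A meeting counted by enrolment need not wait for that.

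**The two reporting sections side by side.** A serious event of a kind that section 7.3 lists as a known complication may be judged expected. Under 7.1.4 it must still be telephoned in within 24 hours and sent to the ethics board. Under 7.1.3 the stated criterion for the Project Manager is not met. The written form in 7.1.4 is conditional and titled for unexpected events. What can be omitted is the central form; the report itself cannot.

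**Cost of a trigger.** If a second case across sites convenes the board, the chance over 100 patients at 1% is 1 − 0.99^100 − 100 × 0.01 × 0.99^99 = 1 − 0.3660 − 0.3697 = 26.4%, for meningitis alone.

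**The case against.** A reader might infer that events after patient 50 are seen by no one with an oversight role. The documents do not support that. Each site's ethics board receives its SAEs, the Project Manager is telephoned within 24 hours, the local investigator signs off catheter-related AEs, and the lead team can see data from all sites. What remains is that each ethics board gets its own site's reports and the lead team is not independent.

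A reader might also infer that a serious but expected case of meningitis could go unreported. It could not: section 7.1.4 is unconditional on the telephone report, and 7.1.3 can be read as describing a subset. The defect is confined to a mismatched criterion and one form.

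The 4.2% figures should not be taken as the likely case. Section 7.3.4 notes that two-thirds of those infected in that series had earlier drainage procedures or CSF fistulae. If CAMPER's zero complications are set against the 91 patients reported in section 2.4 (an assumed denominator), the two-sided 95% upper limit is 1 − 0.025^(1/91) = 4.0%, though with shorter catheter time and no drainage.

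A board charter may provide for extra meetings and for forwarding SAEs. None is shown, and the protocol neither mentions nor rules out such provisions. The point is therefore limited to what the protocol itself fixes. Finally, an early look at 10 patients is a reasonable check for gross procedural problems; that it cannot bound a 1% rate is not an error.

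**Conclusion.** The point holds in limited form. The protocol schedules no independent cross-site safety review for patients 51 to 100, gives no SAE route to the board, states two different criteria for central SAE reporting, and leaves drainage out of the board's remit. At the protocol's own 1% rate, the chance that the unscheduled half contains at least one meningitis case is 39%, and two or more cases 9%. The upper illustration at 4.2% gives 88% and 63%. These figures assume independent patients and constant risk, cover meningitis only, and show the size of the gap without predicting an event rate. This is an inexpensive improvement to patient safety. It does not show that events go unseen, and a charter could already close part of the gap.

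**What to change.** - **Section 7:** count the looks at 10 and 50 by patients who have completed the period to 24 hours after catheter removal. Add one look in the second half, for example at 75. Add CSF drainage to the board's remit. The 75 is a convenient choice, not a derived one; it still leaves 25 patients, with a 1 − 0.99^25 = 22% chance of at least one case at 1%, which is why the next item is needed as well.
- **Section 7.1.4:** have the Project Manager forward each SAE rated possibly or probably related to the catheter or to drainage to the board chair on receipt, and convene the board out of schedule on a second such related event across sites. Limiting this to related events keeps ordinary complications of acute spinal cord injury from setting it off. The board decides what follows.
- **Section 7.2:** the heading covers drainage but the relationship definitions name only the catheter; extend them so that the forwarding rule works for drainage events.
- **Sections 7.1.3 and 7.1.4:** reconcile them so that all SAEs are reported centrally on one form, with a title to match.

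The cost is protocol and, if there is one, charter wording, one short extra meeting, and forwarding of reports already due within 24 to 48 hours. The downside is an occasional unscheduled meeting: about 26% over the trial for meningitis alone at a true 1% rate, and more once the other listed events are counted, by an amount the protocol's figures do not allow one to calculate.
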